#### Study conclusion

Patient participation in the study will conclude at 36 weeks’ corrected GA or at discharge, whichever comes first.

#### Outcomes

The primary outcome is treatment failure (as defined above). We will capture important secondary outcomes, including short- and longer-term respiratory morbidities (Additional file 3: Table S1).

With a birth to hospital discharge time horizon, a cost-effectiveness analysis from the perspective of the health-care system was planned a priori and will be conducted alongside the RCT. From a health-care sector perspective, cost-effectiveness analyses include formal health sector (medical) costs, such as those paid by a third party such as government or a private insurer [24].

#### Sample size

Using data from other recent large neonatal randomized trials with similar populations, including the SUPPORT trial and the COIN trial [9, 10], as well as contemporary data within the NCH-NRN, we estimate that the proportion of patients experiencing respiratory failure in the control arm (FP-CPAP) will be 50%. Based on preclinical work, we estimate the failure rate in the Seattle-PAP arm will be 30% [13, 17]. Accounting for two interim analyses, 200 neonates are needed with a two-tailed type I error rate of 0.05 and a power of 80% [25]. Multiples will be randomized as a set to the same study arm, requiring an inflation of the estimate by 1.12 to allow for the design effect due to clustering [26, 27]. Thus, the calculated sample size is 115 infants per treatment arm.

#### Data collection

Except for data related to the screening log, all remaining clinical data will be obtained from the electronic medical records (Additional file 4: Table S2).

Routinely available costs of inpatient stay will be sourced from the hospital costing units. Direct medical resource utilization will be ascertained through collection of itemized billing records and UB-04 forms, a uniform billing statement recommended by the National Uniform Billing Committee and utilized for reporting of hospital expenditures by third-party payers including the Centers for Medicare and Medicaid Services (CMS). We will convert hospital-reported charges to costs by applying the appropriate CMS cost center specific ratio of costs to charges. Total hospital costs will be the sum of the product of the number of days in each cost category and the calculated per diem costs. Physician professional fees for the initial hospitalization will be based on CMS reimbursement levels for each day of stay and non-bundled procedures.

### Safety

#### Data and safety monitoring board

We have assembled a data and safety monitoring board (DSMB) to protect study subjects and monitor the overall conduct of the trial. Prior to study commencement, the four-person DSMB agreed to the following activities: (1) review the protocol and amendments; (2) participate in the development, finalization, and approval of the DSMB charter; (3) recommend discontinuation of the trial for safety reasons; (4) recommend changes to the study protocol (amendments) for safety reasons; (5) evaluate emergent safety information, evaluate any risk, and identify any potential safety concerns for study patients; (6) request additional data not included in reports, if deemed necessary for effective safety monitoring; (7) communicate DSMB findings and recommendations (to stop, continue, or modify the study) to the site principal investigator (PI; [name]); and (8) provide written minutes following scheduled and ad hoc meetings.

Adverse events and their relationship to study, severity, time of experience, expectation, actions taken to resolve the event, and final outcome will be recorded. All serious adverse events (SAEs) will be sent within 48 h to the DSMB and local IRB. A SAE for this study is any untoward medical occurrence that is believed by the investigators to be causally related to the study intervention and results in any of the following: a life-threatening condition (that is, immediate risk of death), severe or permanent disability, or prolonged hospitalization. SAEs occurring after a subject is discontinued from the study will not be reported, unless the investigators feel that the event may have been caused by the study device. All SAEs will be followed until a satisfactory resolution is achieved or until the health-care provider responsible for the care of the participant deems the event to be chronic or the patient to be stable. All expected and unexpected SAEs, whether or not they are attributable to the study intervention, will be reviewed by the site PI ([name]) to determine if there is a reasonable suspected causal relationship to the intervention. If the relationship is reasonable, SAEs will be reported to DSMB and local IRB for consideration.

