#### Blinding

Blinding of the allocated treatment is not feasible, as the mode of respiratory support is apparent to health-care professionals and families. However, statisticians performing the data analyses will be blinded to group assignment. All enrolled neonates will be given clinical care according to established guidelines, including weaning, extubation, and reintubation [23]. Moreover, the primary outcome (respiratory failure, as defined below) is based on an objective set of criteria applied to both groups.

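### The SAE definition omits death and requires unblinded attribution to the device, and the reporting rules contradict each other, so expedited SAE reports cannot be relied on to show an excess of harm

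*Protocol article*

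**What the plan says.** All but the blinding statement and the interim analyses comes from the section of the protocol article headed Data and safety monitoring board.

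- **Definition, causality.** An SAE is "any untoward medical occurrence that is believed by the investigators to be causally related to the study intervention".
- **Definition, seriousness.** The event must also result in "a life-threatening condition (that is, immediate risk of death), severe or permanent disability, or prolonged hospitalization". Death is not named.
- **First reporting rule.** "All serious adverse events (SAEs) will be sent within 48 h to the DSMB and local IRB".
- **PI review.** "All expected and unexpected SAEs, whether or not they are attributable to the study intervention, will be reviewed by the site PI".
- **Second reporting rule.** "If the relationship is reasonable, SAEs will be reported to DSMB and local IRB for consideration".
- **After discontinuation.** SAEs are not reported unless the investigators think the device may have caused them.
- **Adverse events in general.** "Adverse events and their relationship to study, severity, time of experience, expectation, actions taken to resolve the event, and final outcome will be recorded".
- **DSMB powers.** The board may "request additional data not included in reports, if deemed necessary for effective safety monitoring".

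The Blinding section states: "Blinding of the allocated treatment is not feasible, as the mode of respiratory support is apparent to health-care professionals and families". Only the analysing statisticians are blinded.

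The Interim analysis section reports that the DSMB compared the arms on efficacy, safety and futility after 25 and 110 infants. Both analyses were finished by January 2018. It also mentions safety reviews without describing them.

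**The concern.** Seriousness and causality are separate questions, and this definition merges them. An infant can suffer a life-threatening event and have no SAE because clinicians put it down to prematurity. In this population that explanation is often available. A device effect on common complications of prematurity would then show as an imbalance between arms, and could rarely be recognised in a single infant. Filtering by individual attribution removes the events on which such a comparison depends. Those making the attribution know which device the infant is on, so the filter may also act differently in the two arms.

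The omission of death adds to this. Death is not a component of treatment failure either (section on clinical and respiratory guidelines), so the primary comparison does not capture it.

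The article says safety data in smaller, more immature infants are lacking (Background). It presents the trial as a chance to observe unanticipated SAEs (Discussion). The reporting rule works against that purpose. Because the rules conflict, site staff cannot tell whether to send a death that they think is due to prematurity.

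**Working it through.** The plan gives no SAE or mortality rate, so there is no figure of its own to reproduce. The main check is textual.

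**1. Can the sentences hold together?** There are two ways to read the term SAE.

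| | Literal definition (causality required) | Serious events whatever the cause |
|---|---|---|
| PI review of SAEs attributable or not | Empty for unattributed events, since none can be SAEs | Makes sense |
| All SAEs sent within 48 h | Sends only events believed related | Sends every serious event |
| Sent if the PI finds the relationship reasonable | A second causality filter; the PI can drop an event the investigators attributed, against the 48 h rule | Sends only related events, directly against the 48 h rule |
| Post-discontinuation exception | Excludes nothing, since every SAE is already believed device-caused | Makes sense |
| The written definition | Kept | Contradicted |

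Neither reading makes all the sentences consistent. An unattributed serious event reaches the DSMB as an SAE report only on the second reading with the 48 h rule prevailing, and that goes against both the written definition and the last reporting sentence.

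**2. Is death covered?** A fatal event would usually pass through a life-threatening state, so a death believed related is arguably caught. A death not believed related is not an SAE under the definition.

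**3. How many infants are affected?** Planned enrolment is 115 per arm (Sample size), so 2 × 115 = 230. The second interim analysis followed 110 infants, and 230 − 110 = 120, or 120/230 = 52%. No between-arm safety comparison is described after that point.

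**4. How much can a causality filter hide?** This is an illustration with assumed rates. Suppose the device doubles the serious-event rate, and a fraction f of events in each arm is judged related. With n = 115 per arm, forwarded rates p₁ and p₂, their mean p̄, and a two-sided 5% level:

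power = Φ{(|p₁ − p₂| − 1.96·se₀)/se₁}, where se₀ = √[2p̄(1 − p̄)/n] and se₁ = √[(p₁(1 − p₁) + p₂(1 − p₂))/n].

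For 10% against 20%:

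- f = 1: se₀ = √(2 × 0.15 × 0.85/115) = 0.0471; se₁ = √((0.09 + 0.16)/115) = 0.0466; (0.10 − 0.0923)/0.0466 = 0.165; power 0.57. Expected events are 11.5 and 23.
- f = 0.10, so 1% against 2%: se₀ = 0.01603; se₁ = 0.01602; (0.01 − 0.0314)/0.0160 = −1.34; power 0.09. Expected events are 1.15 and 2.3.

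| True rates | f = 1 | f = 0.5 | f = 0.25 | f = 0.10 |
|---|---|---|---|---|
| 5% vs 10% | 0.30 | 0.17 | 0.10 | 0.06 |
| 10% vs 20% | 0.57 | 0.30 | 0.17 | 0.09 |
| 15% vs 30% | 0.78 | 0.44 | 0.23 | 0.12 |

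The filter is equal in both arms here, so the loss comes from fewer events alone; unblinded attribution could add bias. The calculation ignores clustering of multiples, and the normal approximation is rough at the smallest counts. It describes a comparison made only on forwarded SAEs, not what the DSMB actually saw.

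**The case against.** The strongest reply is that only one channel is filtered. Adverse events are recorded with relatedness as a data item, so causality does not gate recording. The DSMB can ask for data outside its reports. It compared the arms on safety twice, and the article refers to safety reviews besides. Nothing says those comparisons were limited to events judged related. The DSMB charter and the additional files on secondary outcomes and collected data are not shown and may well cover mortality.

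This stands against a stronger reading. A reader might infer that the DSMB was never given the events from which an excess of harm would be seen, or that the interim safety comparisons were filtered in the same way. The article does not support either inference. It does not say which events fed those comparisons, so it shows neither that deaths and unattributed events were included nor that they were withheld. Nor can missed deaths be counted from it: that needs an assumed mortality rate and the further assumption that every death was attributed to prematurity.

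The reply does not repair the stated definition or the conflicting rules, which are on the page and not left to a charter. A right to request data helps only if the board knows what it has not been sent. Both described comparisons are also complete, with about half the infants still to be enrolled after the second.

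It can also be said that the device had regulatory clearance, that the arms differ primarily in the bubbler, and that neither the primary analysis nor the type I error is touched. That is fair, and limits the point to safety reporting.

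**Conclusion.** The point holds for individual SAE reporting. The definition omits death and makes attribution by unblinded investigators a condition. The section contradicts itself on whether unattributed SAEs exist, and on whether all SAEs or only those the site PI finds reasonably related go to the DSMB and IRB. These conclusions rest on the text alone.

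It follows that expedited SAE reports cannot be relied on to reveal an excess of deaths or serious events in one arm. This weighs most on the roughly 120 of 230 infants (52%) enrolled after the second interim analysis, because no later between-arm safety comparison is described. Over the assumed rates, power on forwarded events falls from 0.30–0.78 with no filter to 0.06–0.12 when a tenth are judged related. Those figures show how a filter acts; they do not estimate what happened in this trial. Whether the DSMB's interim comparisons were affected cannot be settled from the article.

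**What to change.** Amend the one paragraph:

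1. Define an SAE by seriousness alone, and add death to the listed outcomes.
2. Record causality as a separate field that does not gate reporting.
3. Reconcile the sentence sending all SAEs within 48 h with the closing conditional sentence by removing PI attribution as a condition for forwarding. The PI may still review and record an opinion.
4. Bring the post-discontinuation sentence into line with the new definition.
5. Give the DSMB all SAEs and deaths by arm at its safety reviews, including infants already enrolled. If the charter already provides this, a cross-reference is enough.

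The cost is a short amendment and longer safety listings. Apart from the screening log, clinical data come from the electronic medical records (Data collection), so little new collection should be needed. The downside is more reports for the DSMB to read, many of them describing expected complications of prematurity.

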#### Interim analysis

Interim analyses were conducted by the DSMB following the enrollment of 25 and 110 infants, respectively. The analyses compared the two groups with respect to efficacy, safety, and futility. A Haybittle–Peto stopping guideline was set at *P* < 0.001 for each interim analysis. The interim analyses were completed in June 2017 and January 2018. Based on these analyses, and on safety reviews conducted to date, the DSMB recommended that the trial continue without modification.

#### Duration of study

The projected duration of the study is 3 years, including 2½ years for subject recruitment.

#### Training of clinical staff

Comprehensive education and training were undertaken to ensure technical proficiency and compliance with the intervention and study protocol at all sites. The site PI ([name]), study coordinator ([name]), and nursing leadership on the study ([name] and [name]) ran a boot camp at the start of the study for all participating sites, with mandatory attendance for physicians, respiratory therapists, and nursing staff to accomplish the following: (1) review differences between the Seattle-PAP and the conventional FP-CPAP devices; (2) identify areas for device troubleshooting; (3) demarcate study goals and objectives; and (4) review safety protocols, procedures, and guidelines for clinical and respiratory care. This effort was intended to optimize reproducibility and consistency. All centers received detailed written instruction on study protocol. The PI and study coordinator were available 24 h each day to answer any questions or concerns.

#### Data management, processing, monitoring, and security

The data generated in this study will be appropriately documented and checked for validity and accuracy. The data will be entered into a database, then the data will be matched and checked for validity and accuracy by a second person before being endorsed for analysis. A record of all discrepancies and resolutions will be kept by the study coordinator ([name]). Outlier data will be investigated. Data will be primarily managed using REDCap (Research Electronic Data Capture) [28]. REDCap is a secure web-based application designed to support data capture in clinical studies. All data with identifiers will be stored on firewall-protected secure servers. Study monitoring visits are performed by the sponsor and their representatives after the enrollment of 50, 100, 150, and 200 infants, and upon the closure of the study.

### Statistical analysis

#### Clinical outcomes

Analyses will be performed using Statistical Analysis Software (SAS) Enterprise Guide version 7.15 (SAS Institute Inc., Cary, NC, USA) using an as randomized (intention-to-treat) principle to compare the primary outcome between treatment arms. Continuous data will be expressed as means with standard deviations or as medians with ranges, whereas categorical variables will be expressed with frequencies and proportions. The primary outcome, and other binary outcomes occurring in at least 5% of patients, will be analyzed using Pearson chi-squared tests. Less common binary outcomes will be compared using Fisher’s exact tests. Risk differences and the number needed to treat, along with their 95% Newcombe hybrid score confidence intervals will be calculated, and risk ratios, and their 95% Koopman asymptotic score confidence intervals, will also be calculated. Normally distributed, continuous outcomes will be compared using Student’s *t*-test, whereas the Wilcoxon rank-sum test will be used to compare continuous outcomes with skewed distributions.

In additional analyses, log binomial regression models will be used to evaluate heterogeneity in the effect of treatment with Seattle-PAP on the primary outcome. Treatment effect heterogeneity will be explored across several clinical characteristics that are known to be associated with CPAP treatment failure: GA, birth weight, and exposure to antenatal corticosteroids [15]. Treatment effect heterogeneity will be tested by evaluating the significance of interactions between the factors of interest and treatment arm in log binomial regression models that include the factor, treatment arm, and their interaction. Effect estimates within subgroups defined by these factors will be expressed as risk ratios with maximum likelihood-based 95% confidence limits. Regression models will be estimated using generalized estimating equations to account for the inherent correlation expected with multiples [27].

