#### Randomization

Enrolled eligible infants are randomly assigned to one of two treatment arms (Seattle-PAP vs. FP-CPAP) (Fig. 3). The allocation sequence is generated using an online, computer-generated randomizer (https://sealedenvelope.com), with a block size of 6, stratified by GA (27–29^6/7^ and 22–27 weeks’ GA). We did not stratify by site, as the treatment of premature neonates is based on shared guidelines throughout the NCH-NRN [23]. Multiple gestations (twins or triplets) are assigned to the same treatment arm.

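### The primary chi-squared test and its score intervals treat infants as independent although multiples are randomised as a set, so the stated 5% error rate is not assured

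*Protocol article*

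**What the plan says.** - **Allocation** (Randomization): "Multiple gestations (twins or triplets) are assigned to the same treatment arm". For these infants the randomised unit is the birth set. Randomisation is stratified by GA in two strata, with blocks of 6.
- **Sample size** (Sample size): "Multiples will be randomized as a set to the same study arm, requiring an inflation of the estimate by 1.12". The starting figure is 200 infants for 50% versus 30% failure, two-sided 5% error and 80% power. The final figure is 115 per arm.
- **Primary test** (Clinical outcomes): "The primary outcome, and other binary outcomes occurring in at least 5% of patients, will be analyzed using Pearson chi-squared tests".
- **Intervals** (Clinical outcomes): "Risk differences and the number needed to treat, along with their 95% Newcombe hybrid score confidence intervals will be calculated". The Koopman score method is named for the risk ratio.
- **Other clinical outcomes** (Clinical outcomes): Fisher's exact test for rarer binary outcomes; Student's t-test or Wilcoxon rank-sum test for continuous ones.
- **Where clustering is handled**: "Regression models will be estimated using generalized estimating equations to account for the inherent correlation expected with multiples". For clinical outcomes, regression models appear only as additional analyses of effect heterogeneity. Their subgroup effects are to be "expressed as risk ratios with maximum likelihood-based 95% confidence limits". The cost model under Economic outcomes also allows for clustering among twins.

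**The concern.** The design and the primary analysis make different assumptions about the same infants. The sample size section accepts that infants from one pregnancy are positively correlated and share an arm, and puts a figure on the resulting variance. The primary test and both interval methods then use a variance that assumes no such correlation. If outcomes within a set are alike, that variance is too small for the effect of clustering.

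At stake are the confirmatory p-value and the headline intervals for the risk difference, number needed to treat and risk ratio. The same mismatch affects the Fisher, t and Wilcoxon comparisons.

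**Working it through.** **Inputs from the protocol article:** failure rates 50% and 30%, two-sided error 0.05, power 80%, design effect (DE) 1.12, 115 per arm, GA stratification in blocks of 6. **Not given, so assumed:** share of infants in twin pairs, intracluster correlation (ICC), and failure rate in each GA stratum.

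**1. Reproduce the sample size.** Two proportions, pooled variance under the null:

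n = [1.96·√(2·0.40·0.60) + 0.8416·√(0.25 + 0.21)]² / 0.20² = 93 per arm. With continuity correction it is 103 per arm (206 in total, close to the stated 200). Then 103 × 1.12 = 115.4, which matches 115 per arm. The inflation for clustering is therefore really in the planned number.

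**2. Effect of ignoring clustering alone.** If the true variance is DE times the naive one:

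- Type I error = 2·[1 − Φ(1.96/√1.12)] = 0.064.
- Coverage of a nominal 95% interval = 1 − 0.064 = 93.6%.
- Interval width relative to the correct one = 1/√1.12 = 0.945, so about 5.5% too narrow.
- Naive p-value that corresponds to a true 0.05 = 2·[1 − Φ(1.96·√1.12)] = 0.038.
- Risk-difference half-width at 50% versus 30%: 1.96·√(0.46/115) = 12.4 points naive; 1.96·√(1.12·0.46/115) = 13.1 points adjusted.

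For DE from 1.05 to 1.20 the error runs from 5.6% to 7.4%.

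**3. Effect of also ignoring the GA strata.** The chi-squared test uses the pooled variance p(1 − p). Stratified randomisation removes most of the between-stratum part of it, so the test overstates that part. Assume two equal strata with mean failure rate 0.40 (pooled variance 0.24), and DE 1.12 (for example 30% of infants in twin pairs and ICC 0.4: 1 + 0.30 × 0.4). If balance were perfect, the net ratio of true to naive variance would be 1.12 × (average within-stratum variance)/0.24:

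| Assumed stratum failure rates | Average within-stratum variance | Net variance ratio | Error by formula | Error in simulations |
|---|---|---|---|---|
| 40% / 40% | 0.2400 | 1.120 | 6.4% | 6.2% to 7.0% |
| 30% / 50% | 0.2300 | 1.073 | 5.9% | 5.6% to 6.0% |
| 25% / 55% | 0.2175 | 1.015 | 5.2% | 5.2% to 5.6% |
| 20% / 60% | 0.2000 | 0.933 | 4.2% | 4.5% to 4.7% |

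The last column gives the range over separate simulation sets with 230 infants, families randomised in blocks of 6 within stratum, and the unadjusted test. One set ran from 6.2% (40/40) to 4.6% (20/60). Monte Carlo standard errors were about 0.2 points where 12,000 trials were run. With no twins and equal strata the rejection rate was 5.2%. Holding the total rather than the within-stratum ICC at 0.4 lowered the last three rows to 5.9%, 5.2% and 4.3%.

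**4. Power after a matching analysis.** Effective size = 115/1.12 = 102.7 per arm, which gives about 84% power for 50% versus 30% (normal approximation without continuity correction). This is still above 80%.

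**The case against.** **The error may not exceed 5% at all.** A reader might infer from step 2 that the type I error is simply 6.4%. The documents do not support that. The Clinical outcomes section itself lists GA among characteristics known to be associated with CPAP failure, and randomisation is stratified on it. An unstratified test is then conservative on that account, and step 3 shows that the two effects can cancel or reverse. This objection stands against any flat claim of inflation. It does not make the analysis valid: error control would rest on an accidental balance between two features that the test ignores.

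**The effect is small.** This stands. Even with no offset, the shift is 1.4 points of type I error and 0.7 points of half-width, and only p-values of roughly 0.038 to 0.05 would change sides. The estimated risk difference does not move.

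**The 12% inflation is wasted.** A reader might infer this, but it is wrong. The extra infants add precision whatever test is used; what is missing is the matching variance.

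**Every interval is affected.** This also goes too far. GEE is named for the subgroup models, and the cost model allows for twins.

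**The GEE sentence, or an unseen analysis plan, covers the primary test.** It does not. A Pearson chi-squared test is not a regression model, and the article names the primary test and both interval methods outright. This is a stated choice, not a detail left for later.

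**Conclusion.** The point holds as a mismatch between design and primary analysis. Sets are randomised together and the sample size allows for it, but the primary test, its intervals and the simple tests for other clinical outcomes do not.

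The size is modest. The figures of 6.4% error, 93.6% coverage and 5.5% narrowing describe clustering alone and rest on the protocol's DE of 1.12 being right. The net error depends on stratum failure rates, twin share and ICC, which the article does not give. Under the values tried it lay on either side of 5%, so the supported conclusion is that 5% is not assured, not that it is exceeded.

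A separate, minor point: the subgroup limits are described as likelihood-based although the models are to be fitted by GEE, which has no likelihood. This is a wording conflict in exploratory analyses and adds nothing to the primary point.

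Severity: should-fix.

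**What to change.** 1. **Primary analysis.** Use a GEE with infants clustered by birth set, treatment and GA stratum (as used in randomisation) in the model, and robust standard errors. Take the primary p-value from it.
2. **Effect measures.** Take the risk ratio from a log link. A log link does not give a risk difference directly, so obtain the risk difference and number needed to treat from an identity link or by standardisation. Report cluster-robust 95% intervals for all of them, in place of the Newcombe and Koopman intervals.
3. **Other clinical outcomes.** Use cluster-adjusted methods where event counts allow.
4. **Chi-squared test.** Keep it as a descriptive check only.
5. **Heterogeneity models.** Replace the likelihood-based limits with robust limits.

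**Cost:** changes of wording in the protocol and analysis plan, and a small amount of programming with a method that the plan already names. The p-value and intervals may become slightly less favourable. No extra infants or data are needed, because the planned 115 per arm already allows for the adjustment. The article describes recruitment as ongoing and the statisticians as blinded to group assignment, so the change should be fixed in writing before the final analysis.

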These observations led to a recent study that compared Seattle-PAP and conventional bubble nCPAP (FP-CPAP) among premature infants with an average GA of 29 weeks. The authors observed, among 40 neonates, reduced breathing effort with Seattle-PAP than with FP-CPAP; however, the study was not designed to detect important clinical differences between the two devices [13]. To recommend Seattle-PAP over the current standard of care (bubble nCPAP), a larger comparative trial is needed. Thus, the present study is designed to compare the incidence of respiratory failure over the first weeks of life between the two groups. While the present study is not designed to determine differences in longer-term clinical outcomes (BPD), prespecified secondary analyses are planned.

We acknowledge a number of challenges in the design of the trial. First, the potential benefits and risks of Seattle-PAP versus conventional bubble nCPAP (FP-CPAP) may not be uniform across infants born at all GAs. To that end, we determined a priori to perform a subgroup analysis on infants born after <27 weeks versus those born after 27 to 30 weeks of gestation. Second, our recruitment window provides enrollment up to 72 h of life, irrespective of previous respiratory support (mechanical ventilation or CPAP) and likely over a wide range of acutely impaired lung function. We recognize that this potential heterogeneity increases the risk of type II errors [36]. Third, some infants allocated to Seattle-PAP may receive a brief period of FP-CPAP prior to randomization, which conceivably could affect the interpretation of the results. We attempted to restrict the impact of this by excluding from the trial infants who have received more than 72 h of FP-CPAP, which we felt to be the shortest window in which seeking parental consent would be feasible. Finally, blinding of the interventions, which would have been preferable from a study design perspective, was not feasible, due to the complexity of building and operating a system that disguised which device was providing respiratory support to the infant, yet allowed the clinical care team to monitor effective engagement of the infant with the pressure-generating system.

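### Allocation is stratified by gestational age but the primary chi-squared test and its intervals ignore the strata, which makes them conservative from this source; the printed gestational-age bounds also need reconciling

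*Protocol article*

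**What the plan says.** - **Randomization.** The allocation list is built "with a block size of 6, stratified by GA". The two strata are printed as "stratified by GA (27–29^6/7^ and 22–27 weeks’ GA". Multiples go to the same arm.
- **Clinical outcomes.** The primary outcome, like other binary outcomes that are not rare, "will be analyzed using Pearson chi-squared tests". The effect measures are likewise unstratified: "Risk differences and the number needed to treat, along with their 95% Newcombe hybrid score confidence intervals will be calculated", and the risk ratio gets a Koopman interval. GA enters only the additional interaction models, which are log binomial models fitted by generalized estimating equations (GEE). There it is listed among factors "known to be associated with CPAP treatment failure: GA, birth weight, and exposure to antenatal corticosteroids".
- **Sample size.** Failure is put at 50% on control and 30% on Seattle-PAP, with two-sided 5% error and 80% power. This gives 200 infants, raised by a factor of 1.12 for multiples to 115 per arm.
- **GA bounds elsewhere.** The inclusion criteria run to 30 completed weeks. The Abstract, Aims, Study settings, Recruitment and Randomization sections all end at 29 6/7. The Discussion announces a "subgroup analysis on infants born after <27 weeks versus those born after 27 to 30 weeks of gestation".

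**The concern.** Blocked randomisation within strata forces the arms to be nearly balanced on GA, so differences in risk between the strata no longer contribute to chance variation in the treatment difference. The ordinary chi-squared test does not know this. Its variance is computed as if GA balance had been left to chance, so it is too large whenever GA predicts failure, and the article itself says that it does. The result is a test that rejects too seldom under the null and intervals wider than the design warrants. Some power that a stratified analysis would deliver is left unused.

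The strata themselves are also not cleanly stated. Week 27 appears in both, and the inclusion list, read literally, admits an infant at 30 weeks for whom no stratum exists. An analysis by stratum needs an unambiguous stratum for every infant.

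**Working it through.** **1. The plan's own figure.** For 50% against 30%, two-sided 5% and 80% power, the standard two-proportion formula gives 93 per arm (186) without continuity correction and 103 per arm (206) with it. The latter is within 3% of the stated 200, and 206 × 1.12 = 230.7 matches 230. The literal product 200 × 1.12 is 224. The sample size is therefore reproduced closely enough.

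**2. Inputs.** From the article: 50% and 30% (risk ratio 0.30/0.50 = 0.6), 115 per arm and design effect 1.12, so the effective n is 115/1.12 = 102.7 per arm. Assumed, because the article gives neither stratum rates nor stratum shares: two equal strata, the same risk ratio of 0.6 in both, and control rates of 60/40, 70/30 or 75/25 (lower/higher GA), each averaging 50%.

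**3. Type I error from ignoring strata.** Under the null, let r be the mean within-stratum p(1−p) divided by the unstratified 0.50 × 0.50 = 0.25. Actual size = 2[1 − Φ(1.96/√r)].

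| Control rates | mean p(1−p) | r | Actual size |
|---|---|---|---|
| 60/40 | 0.2400 | 0.96 | 4.5% |
| 70/30 | 0.2100 | 0.84 | 3.2% |
| 75/25 | 0.1875 | 0.75 | 2.4% |

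**4. Power at 230 infants.** The unstratified standard error is SE_u = √[(0.25 + 0.21)/102.7] = 0.0669. The standard error under stratified allocation, SE_s, uses the mean within-stratum p(1−p) in each arm. The chi-squared test divides by SE_u, but its estimate actually varies with SE_s, so:
- unstratified power = Φ[(0.20 − 1.96 × SE_u)/SE_s]
- stratified power = Φ[0.20/SE_s − 1.96]

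| Control rates | Sum of arm variances (control + treatment) | SE_s | Unstratified | Stratified | Gain (points) |
|---|---|---|---|---|---|
| 60/40 | 0.2400 + 0.2064 = 0.4464 | 0.0659 | 85.2% | 85.8% | 0.7 |
| 70/30 | 0.2100 + 0.1956 = 0.4056 | 0.0629 | 86.3% | 88.9% | 2.6 |
| 75/25 | 0.1875 + 0.1875 = 0.3750 | 0.0604 | 87.3% | 91.1% | 3.9 |

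Gains are taken before rounding. The unstratified variance estimate is too large by 0.46/0.4464 = 1.03, 0.46/0.4056 = 1.13 and 0.46/0.375 = 1.23. By the square root, intervals are roughly 2%, 6% and 11% too wide.

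**5. Simulation check.** 60,000 trials per scenario were run with blocks of 6 in two equal strata, 230 infants, a common odds ratio and no multiples. The unstratified test was compared with a GA-stratified Cochran-Mantel-Haenszel test. Type I error at 60/40, 70/30 and 75/25 was 5.1%, 3.7% and 2.8% unstratified, against 5.2%, 4.9% and 4.9% stratified. Power was 88.4%, 89.8% and 90.7% against 88.8%, 92.2% and 94.3%. Power is higher than in step 4 because clustering was left out. Direction and order of magnitude agree.

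**6. The opposing effect of multiples.** The chi-squared test also ignores clustering. With design effect 1.12 alone, size = 2[1 − Φ(1.96/√1.12)] = 6.4%. Multiplying the two variance ratios, 1.12 × r = 1.075, 0.941 and 0.840, gives a net size of about 5.9%, 4.3% or 3.2%. This is an approximation that treats the two effects as separate.

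**7. GA bounds side by side.** Strata in Randomization: 22–27 and 27–29 6/7, so week 27 is in both. Discussion: below 27 against 27 to 30. Inclusion criteria: 22 to 30 completed weeks. Other statements of the population: 22 0/7 to 29 6/7. These cannot all be literally right.

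**The case against.** The strongest defence is that little harm is shown. The fault is conservative, power exceeds the planned 80% in every scenario, and at 60/40 the effect is negligible. Its size rests wholly on assumed stratum rates. All of that stands.

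Three stronger readings are tempting, and the article does not support them.
- A reader might infer that a test with the wrong error rate risks false positives. From the strata alone it does the reverse. A size above 5% can arise only through the ignored multiples, which is a separate matter.
- A reader might infer that the benefit of stratifying is thrown away. It is not. GA balance still reduces the true variance of the unstratified risk difference, so unstratified power also rises with the strength of GA, from 85.2% to 87.3% above. Holding it at the 84.8% that SE_u alone would give, Φ(0.20/0.0669 − 1.96), overstates the loss. What is missed is that the reported standard error and interval do not show the gain.
- A reader might infer that infants were misallocated or wrongly enrolled because of the GA bounds. The Discussion's wording points to a cut at 27 weeks and uses 30 loosely, so a drafting slip is plausible. No effect on the primary result is shown.

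It might also be said that such detail belongs in an analysis plan that is not shown. That does not stand, because the article itself names the primary test and the intervals. Finally, recruitment is under way and both interim analyses are complete, so a change to the primary analysis has a procedural cost.

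**Conclusion.** The mismatch is real: GA is used to randomise and acknowledged as prognostic, then left out of the primary comparison. Its consequence is lost efficiency and a conservative test, small if GA is weakly prognostic and material from about 70/30. Under the stated assumptions, size falls to about 4.5%, 3.2% or 2.4%, and 0.7, 2.6 or 3.9 points of power go unused. The sample size is not undermined. Together with unmodelled multiples, the net size could be about 5.9%, 4.3% or 3.2%, and the article does not determine which. The GA bounds are a genuine contradiction, but one of wording to be reconciled. The textual facts are certain; the magnitudes depend on stratum rates and shares that the article does not give.

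**What to change.** Analyse the primary outcome with the GA stratum as randomised. The binomial GEE approach already planned for the additional analyses would serve, with treatment and stratum as terms and multiples as clusters, which addresses both variance problems at once. Report the stratum-adjusted risk difference and risk ratio with matching intervals. The unadjusted comparison can remain as a supporting analysis.

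Separately, reconcile the strata in Randomization, the subgroup cut in the Discussion, and the upper GA bound in the inclusion criteria against the other statements of the population. Check them against the allocation list as actually run, and state strata that do not overlap and that cover every eligible infant.

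The cost is one covariate that randomisation already required, some rewording, and a documented amendment made before unblinded final analysis.
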